Perceptions about splint wearability, especially comfort and satisfaction require attention as well. Out of 10 studies about splint for TF, only two studies had investigated the splint wearability (Drikoningen et al. 2017; Tarbhai et al. 2012). Tarbhai et al. (2012) compared 6 weeks of full time wear of MCPJ blocking splint to DIPJ blocking splint in two evenly matched cohorts. After six weeks of MCPJ blocking splint wear 10/13 digits were fully or partially improved compared to 7/15 digits managed with a DIPJ blocking splint. Initially before splint wear both TF groups reported no loss of hand function but after wearing their respective splints reported it was awkward to work. Additionally, after splint wear, patient-rated function for the MCPJ blocking splint was 'good' (n=7/13) and 'fair' (n=5/13), while 7/15 DIPJ blocking splint wearers rated equally as 'good' or 'fair'. More patients (n=10/13; 77%) rated the MCPJ blocking splint as comfortable than 9/15 (60%) patients in the DIPJ blocking splint group. Stiffness of the PIPJ was also a concern with those who wore the DIPJ blocking splint. The author's recommendation was to use the MCPJ blocking splint due to comfort and greater success rate. Although the MCPJ blocking splint showed better results than DIPJ blocking splint, the involved MCPJ was restricted thus, it makes holding objects difficult. Among the comments from participants about MCPJ blocking splint were: 1) awkward hand positions when working; 2) longer time was needed to do things; 3) edges of splint was digging. Drikoningen et al. (2017) had reported mean satisfaction of 5.8 points (SD + 3.3, 10 rating-scale) for six weeks night-wear MCPJ blocking splint. After six week of splint wear, 18 from 34 participants had received corticosteroid injection due to unsatisfied or noncompliance to the splint, or triggering was unable to resolve.

In contrast, the originators of the finger-based RME splint encouraged early use of the injured hand for light tasks such as eating, writing, self-care to prevent the secondary complications of adhesion formation and finger stiffness. Collocott et al. (2020) noted that extensor tendon repair individuals who were from RME group show better hand functions compare to controlled active motion group at four weeks for the Sollerman Hand Function

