### 3.5 Withdrawal criteria

Participants can choose to withdraw at any time. Participants may be withdrawn if the investigator deems that it is detrimental or risky for the subject to continue. Withdrawn subjects will not be replaced by a new participant as we have already included the dropout rate (10%) into our sample size calculation.

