### 3.6 Sample Size

A sampling of convenient method will be used to select eligible patients.

A prior TF research study (Teo et al. 2019) had reported that the result of pain score for pre-treatment = 4.65 (SD 2.39) and post-treatment = 3.40 (SD 2.44). G\*Power was used to compute statistical power analyses. Cohen-d effect size is 0.5175152.

Given Cohen-d effect size needs to be converted into Cohen-f effect size in order to determine the sample size of this study for two ways ANOVA, therefore, after converting digitally, the Cohen-f effect size is 0.259.

This proposed study will need 32 participants when a Cohen-f effect size of 0.26, confident level of 95%, significant level of 5%, and statistical power of 80% is applied.

Since a 10% dropout rate is anticipated, a total of 36 participants will be needed for this study. Of this total, 18 patients will be allocated to the RM group (RMG) and 18 patients to the MCPJ blocking group (MCPJBG).

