For the RME splint, a strip of thermoplastic will be woven around on the proximal phalanx of all four fingers with the MCPJ of the affected finger(s) positioned in approximately 20°-25° more extension than MCPJ of the adjacent fingers. For the RMF splint, the thermoplastic strip will be woven with the MCPJ of the affected finger(s) positioned in approximately 20°-25° more flexion than the MCPJ of the adjacent fingers. The angle of MCPJ will be increased if 20°-25° flexion/extension is not enough to reduce/stop pain or triggering. For MCPJ blocking splint, the thermoplastic material will be moulded to contour the palm over the MCPJ and formed into a circumferential "ring" around the proximal phalanx of the affected finger(s). After the splint was fabricated, the participants will have to wear the splint for 15 minutes to check if the splint has pressure points that can cause pain or any redness of the skin. If there are pain and redness, the splint will be readjusted to prevent these pressure points. For all splints, each participant will be asked to assess the comfort and satisfaction with the splint before leaving the clinic.

The RMG and MCPJBG participants will receive same education and conventional treatment. Each participant will be instructed to wear the splint full time (24-hours) every day and night for six weeks, with the exception that the splint can be removed for hygiene purposes including washing hands and showering. No gripping when out of splint. To track splint wearing adherence, each participant will be given a diary to record the hours the splint was worn in a 24-hour period. Participant will also be asked to record what task(s)he/she has

removed the splint. Each participant will be informed about the condition of TF including symptoms, cause, risk factor, and treatment. Participants will also be encouraged to modify activities that may provoke their TF symptoms while wearing the splint. Suggestions for activity modification include stopping or limiting activities that involve repetitive hand use and prolonged gripping. Participants will be asked to contact the researcher if there are any problems with the splint that affect wear or to replace the splint if participant has accidentally lost their splint. The researcher will arrange an appointment as soon as possible with them to address these problems and make note of this interruption in intervention.

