Each participant will be required to attend three sessions of therapy over the study period of six weeks. These sessions ideally will be the initial therapy session (Week-1), then three weeks later (Week-3), and six weeks after the initial session (Week-6). At Week-3, Therapist B will conduct the VAS assessment (comfort, and satisfaction) and provide the conventional therapy to each participant. Therapist B will perform a deep circular massage over A1 pulley for 5 minutes and each participant will be taught how to do the deep circular massage at home. The researcher will inspect each participant's splint and adjust it accordingly based on the participant's comments.

At Week-6, Therapist A will administer the post-intervention assessment for all participants. Table 1.0 outlines the procedure involved in RMG and MCPJBG. Figure 1.0 is the flowchart of the procedure.

Table 1.0 Procedure involved in Relative Motion Group and Metacarpophalangeal Joint Blocking Group.

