### 3.9 Statistical Analysis Plan

Descriptive statistics will be used to summarize the Demographic data including age, gender, occupation, hand dominance, digit involved, associated medical conditions, and duration of triggering. Data will be analysed and described in total numbers, mean, and the pattern of data. Descriptive statistics will also be used to demonstrate the assessment outcomes including DASH, COPM, VAS (pain, comfort, and satisfaction), Number of Triggering in Ten Active Fists, and SST. An independent sample *t*-test, set at the significant level of 0.05 will be used to compare the baseline data between RMG and MCPJBG. A Two Way Mixed-ANOVA, set at the significant level of 0.05 will be used to compare the assessment outcomes, including DASH, COPM, VAS (pain, comfort, and satisfaction), Number of Triggering in Ten Active Fists, and SST between the RMG and MCPJBG. The interaction effect between these different variables will be analysed too. The results will show the percentage of variance in each effect regardless of size (Hypotheses 1 – 7).

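### The two-way mixed ANOVA fixed for comfort and satisfaction drops anyone who misses a rating visit; a repeated-measures mixed model would keep their ratings and remove a modest possible bias

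*Protocol*

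**What the plan says.** Section 3.9 names one procedure for every outcome: "A Two Way Mixed-ANOVA, set at the significant level of 0.05 will be used to compare the assessment outcomes". VAS comfort and satisfaction are in the list.

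These two outcomes have an intermediate rating. Section 3.8 provides for a rating on Day 1 once the splint is made, when "each participant will be asked to assess the comfort and satisfaction with the splint before leaving the clinic". It then adds a second occasion: "At Week-3, Therapist B will conduct the VAS assessment (comfort, and satisfaction"). The third is the Week 6 assessment. The comfort data form is headed for Weeks 1, 3 and 6. The other outcomes are measured only on Day 1 and at Week 6.

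On losses, section 3.5 says: "Withdrawn subjects will not be replaced by a new participant", because a 10% dropout allowance is built into the sample size. Section 3.6 raises 32 participants to 36 for this reason. The protocol states no analysis set and no imputation rule, and it gives no dropout by arm.

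**The concern.** In a classical mixed ANOVA each participant contributes a full row, one value per level of the time factor. If the Week 6 value is missing, the whole row goes, with the Day 1 and Week 3 ratings in it. This is a property of the method the protocol has chosen, and not merely silence about missing data.

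Comfort and satisfaction are where this matters. The discarded ratings are informative about the outcome, and discomfort is a plausible reason for not returning. If uncomfortable wearers are lost more often, and one splint is less comfortable, complete-case analysis removes more low ratings from that arm. The estimated difference between the splints then shrinks. Hypotheses 6 and 7 are the ones exposed. For outcomes with only two visits, little is gained by a different model.

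**Working it through.** **1. The protocol's own sample size.** Inputs from 3.6: means 4.65 and 3.40, SDs 2.39 and 2.44.

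- d = (4.65 − 3.40) / √((2.39² + 2.44²)/2) = 1.25 / 2.415 = 0.518, and f = d/2 = 0.259. Both agree with the protocol.
- For the group-by-time interaction with two measurements, the noncentrality is λ = f²·N·m/(1 − ρ). With f = 0.26, N = 32, m = 2 and ρ = 0.5 (assumed; the protocol gives none), λ = 0.0676 × 32 × 2 / 0.5 = 8.65 on 1 and 30 degrees of freedom. Power is 0.812, so 32 reproduces.
- 32 / 0.90 = 35.6, so 36 reproduces. (The synopsis says 42, a separate discrepancy on which this point does not depend.)

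The step from 32 to 36 counts a dropout as contributing nothing, which fits a complete-case analysis. On the same formula, power is 0.785 with 30 complete cases and 0.755 with 28.

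**2. Inputs for the bias check.**

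- From section 1.2: satisfaction mean 5.8 and SD 3.3 on a 10-point scale, for a night-worn blocking splint.
- Assumed: true arm difference 2.0; correlation between Week 3 and Week 6 ratings 0.5 to 0.7; logistic loss after Week 3, more likely at low comfort, slope 0.5 or 1.0 per point.
- Overall loss is set to the protocol's 10%. This gives about 6% in one arm and 14% in the other, or 18 × 0.06 = 1.1 and 18 × 0.14 = 2.5 people.

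**3. Results for the Week 6 difference (truth 2.0, 10% loss).**

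| Loss depends on | Complete cases | Mixed model, covariance pooled over arms |
|---|---|---|
| Week 3 comfort (observed) | about 1.7 to 1.9 | about 2.0 |
| Week 6 comfort (unobserved) | about 1.55 to 1.8 | about 1.7 to 1.9 |

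With 18 per arm, root mean squared error in the first row is about 1.15 for both methods. In the second row it is lower for the model.

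**4. Size against sampling error.** With 16 completers per arm, SE = 3.3 × √(1/16 + 1/16) = 1.17. In the first row the complete-case estimates run from 1.70 to 1.88, so the bias is 2.0 − 1.88 = 0.12 to 2.0 − 1.70 = 0.30. That is 0.12/1.17 = 0.10 to 0.30/1.17 = 0.26 standard errors.

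**5. Week 3.** In the first-row setting the complete-case Week 3 difference is 1.58 to 1.75, although every Week 3 rating was collected. Row-wise deletion alone causes this.

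**6. Other assumptions.** At 20% loss, twice what the protocol expects, the complete-case Week 6 difference is 1.56 to 1.80 when loss follows Week 3 comfort. A different set-up (truth 1.5, SD 2.4, correlation 0.3 to 0.7, heavy loss below a comfort threshold) gives 1.17 to 1.44 for complete cases and about 1.5 for an analysis using all visits. The direction is the same.

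**The case against.** **The handling of missed visits belongs in an SAP, which may exist.** It is true that the protocol never says complete cases, and a separate plan could add imputation. But the protocol does fix the test, and row-wise exclusion comes with it. The point is the choice of method, and that stands.

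**Stopping the splint is not a missed rating.** A reader might infer that everyone who gives up an uncomfortable splint leaves the analysis. The documents do not support that: only a missed visit causes exclusion. Section 3.8 also provides a fit check, readjustment and early appointments for splint problems, which may limit loss.

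**The cited cohort does not show dropout by arm.** Section 1.2 reports that "18 from 34 participants had received corticosteroid injection due to unsatisfied or noncompliance to the splint", and the sentence goes on to give unresolved triggering as a further reason. A reader might infer that loss in this trial will depend on comfort and differ between arms. But those injections came after six weeks of night-only wear of one splint type. They were a change of treatment, not missing assessments, and there was no relative motion arm. Loss related to comfort therefore remains an assumption.

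**At this sample size the fix may gain nothing.** This holds for one version of it. An estimator that fits the Week 3 adjustment separately in each arm has a root mean squared error of 1.15 to 1.19, against 1.13 to 1.15 for complete cases. Pooling the covariance over arms removes that penalty.

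**The model's estimate of 2.0 is built in.** It holds only if loss depends on observed ratings. If loss depends on Week 6 comfort, the model removes only part of the bias.

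**Conclusion.** The point holds as a cheap improvement to the analysis of Hypotheses 6 and 7. The stated method discards collected comfort and satisfaction ratings of anyone who misses a visit. A standard alternative uses them with no loss of accuracy in the settings examined.

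The size is modest. At the protocol's 10% loss, with loss driven by Week 3 comfort, the bias is about 0.1 to 0.3 points on a 10-point scale. It is somewhat larger if loss follows Week 6 comfort. In these scenarios the bias is toward no difference, so it would not create a false finding. The figures rest on an assumed difference of 2.0, assumed correlations and an assumed link between discomfort and loss. If loss is unrelated to comfort, the cost is only discarded data.

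A reader might infer that the comfort comparison is invalid or seriously distorted. The documents do not support that, since they give no dropout by arm and expect loss of only 10%.

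**What to change.** In 3.9, for VAS comfort and satisfaction only, replace the two-way mixed ANOVA by a linear mixed model for repeated measures:

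- fixed effects for arm, visit and arm-by-visit;
- unstructured covariance pooled over arms, REML, small-sample degrees of freedom;
- all ratings made after fitting (Day 1, Week 3, Week 6), from all randomised participants in the arm assigned;
- the Week 6 arm difference as the reported result.

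This needs no new visits, data or participants, only a change of wording and a different procedure at analysis. The downside is reliance on missing-at-random given earlier ratings. That is a weaker assumption than the complete-case ANOVA needs, but the model corrects only partly if loss depends on Week 6 comfort that was never observed. A sensitivity analysis for withdrawals attributed to discomfort would show how much this matters.

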## **2.1 HYPOTHESES**

Hypothesis 1: There is a difference in terms of severity staging as measured by Stages of Stenosing Tenosynovitis (SST) between patients diagnosed with TF involving the A1 pulley who are prescribed a RM splint for six weeks and those prescribed a MCPJ blocking splint under the same conditions.

Hypothesis 2: There is a difference in terms of pain as measured by Visual Analog Scale (VAS) between patients diagnosed with TF involving the A1 pulley who are prescribed a RM splint for six weeks and those prescribed a MCPJ blocking splint under the same conditions.

Hypothesis 3: There is a difference in terms of finger triggering as measured by number of triggering events in ten active fists between patients diagnosed with TF involving the A1 pulley who are prescribed a RM splint for six weeks and those prescribed a MCPJ blocking splint under the same conditions.

Hypothesis 4: There is a difference in terms of hand function as measured by Disabilities of the Arm, Shoulder and Hand (DASH) Outcome Measure between patients diagnosed with TF involving the A1 pulley who are prescribed a RM splint for six weeks and those prescribed a MCPJ blocking splint under the same conditions.

Hypothesis 5: There is a difference in terms of occupational performance as measured by Canadian Occupational Performance Measure (COPM) between patients diagnosed with TF involving the A1 pulley who are prescribed a RM splint for six weeks and those prescribed a MCPJ blocking splint under the same conditions.

Hypothesis 6: There is a difference in terms of comfort as measured by Visual Analog Scale (VAS) between patients diagnosed with TF involving the A1 pulley who are prescribed a RM splint for six weeks and those prescribed a MCPJ blocking splint under the same conditions.

Hypothesis 7: There is a difference in terms of satisfaction as measured by Visual Analog Scale (VAS) between patients diagnosed with TF involving the A1 pulley who are prescribed a RM splint for six weeks and those prescribed a MCPJ blocking splint under the same conditions.

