**e. Disabilities of the Arm, Shoulder and Hand (DASH) Outcome Measure**

The Disabilities of the Arm, Shoulder and Hand (DASH) Outcome Measure will be used to measure hand function in this study. DASH is a 30-item, self-report questionnaire designed to assess the patient's health status during the previous week. The DASH consists of 21 items that assess performance of select activities; 5 items assess the severity of symptoms; and 4 items assess the impact of the problem on social function, work, sleep and self-image. Two optional modules specific to work, sports and/or performing arts will not be used in this study. The DASH has a total possible score of 0 to 100 with higher scores represent more severe disability or poorer hand function (Hudak et al. 1996; William 2014). The minimal clinically important difference for the DASH is 10.83 points (Franchignoni et al. 2014). Kleinlugtenbelt et al. (2018) reported excellent internal consistency (Cronbach's  $\alpha=0.97$ ) and excellent test-retest reliability (ICC= $0.91$ ) for the DASH.

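### Section 3.9 does not say which mixed-ANOVA effect tests Hypotheses 1–7, and baseline-adjusted Week-6 ANCOVA would be more precise for pain, DASH and COPM

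*Protocol*

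**What the plan says.** Protocol section 3.9 states: "A Two Way Mixed-ANOVA, set at the significant level of 0.05 will be used to compare the assessment outcomes". The outcomes listed are DASH, COPM, VAS (pain, comfort, satisfaction), triggering events and SST. The next sentence adds: "The interaction effect between these different variables will be analysed too". On reporting it says: "The results will show the percentage of variance in each effect regardless of size", and Hypotheses 1–7 are attached to that sentence as a block. No sentence names one effect as the test of a hypothesis, and no baseline covariate is mentioned. Baseline values are used only in a significance test: "An independent sample *t*-test, set at the significant level of 0.05 will be used to compare the baseline data between RMG and MCPJBG".

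The specific objectives in section 2.2.2 ask for the group comparison after six weeks. Under section 3.8 and Table 1.0, pain, DASH, COPM, triggering and SST are measured on Day 1 before randomisation and again at Week 6. Comfort and satisfaction are also rated after the splint is fitted on Day 1 and at Week 3.

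**The concern.** A two-way mixed ANOVA of group by time yields three tests per outcome: group, time, and group by time. The effect usually called the between-group comparison is the group main effect, which averages each participant's scores over time. With one score taken before randomisation and one at Week 6, that average mixes a score no splint can have influenced with the score of interest. The interaction is the term that matches the objective, and section 3.9 mentions it only as an addition.

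Two things are at stake. An analyst who takes the main effect as the answer would report half the Week-6 difference and would have low power. An analyst who takes the interaction would have a valid test, but one that uses the collected baseline less efficiently than it could, in a trial of 32 analysable participants.

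**Working it through.** **Inputs from the protocol.** Section 3.6 gives f = 0.26, N = 32 before dropout, and "confident level of 95%, significant level of 5%, and statistical power of 80% is applied". Allocation is 1:1, so 16 per arm. There are two measurement times for the five outcomes named above.

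**Assumptions.** The protocol does not state the pre-post correlation rho; I take 0.5, with a range of 0.3 to 0.7. SDs are equal at both times and baselines are equal in expectation. Tests are two-sided at 0.05.

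**1. Reproduce the stated N.** For 2 groups and 2 times, the test has 1 and N − 2 degrees of freedom and noncentrality lambda:

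- Interaction: lambda = f² × N × 2/(1 − rho) = 0.0676 × 32 × 2/0.5 = 8.65. Power is 81.2%, and 32 is the smallest even N that reaches 80%.
- Group main effect: lambda = f² × N × 2/(1 + rho) = 0.0676 × 32 × 2/1.5 = 2.88. Power is 37.6%, and 80% needs N = 90.

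So 32 fits the interaction and not the group main effect. The within-subject time effect uses the same formula as the interaction and also gives 32, so the match does not prove which of those two was meant.

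**2. What each effect estimates.** Let D be the Week-6 difference in SD units.

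| Analysis | Estimates | SD factor |
|---|---|---|
| Group main effect | D/2 | √((1 + rho)/2) |
| Group-by-time interaction | D | √(2(1 − rho)) |
| Week-6 ANCOVA on baseline | D | √(1 − rho²) |

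The standard error is the SD factor × √(2/16). With equal baselines f = D/4, so f = 0.26 means D = 1.04. In 20,000 simulated trials at D = 1.04 and rho = 0.5, the mean estimates were 0.52, 1.04 and 1.04, with standard errors 0.304, 0.353 and 0.309.

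**3. Precision of ANCOVA against the interaction.** The variance ratio is (1 − rho²)/(2(1 − rho)) = (1 + rho)/2. That is 65% at rho = 0.3, 75% at 0.5 and 85% at 0.7.

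**4. Power at 16 per arm for an assumed D = 1 SD** (noncentral t; ANCOVA loses one degree of freedom):

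| rho | Main effect | Interaction | ANCOVA |
|---|---|---|---|
| 0.3 | 40% | 64% | 82% |
| 0.5 | 35% | 78% | 88% |
| 0.7 | 32% | 94% | 97% |

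**5. A smaller difference.** If D were only the 0.5175 that section 3.6 derives from a pre-post change, power at rho = 0.5 would be 13%, 29% and 37%. ANCOVA is still best, but it does not make N = 32 adequate for a difference of that size.

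**The case against.** The strongest reply is that the interaction is already in the plan. It is unbiased and undiluted, results are promised for each effect, and the sample size fits it. On this view the sentence that adds the interaction is loose wording, and one clarifying line would settle the matter. Most of this stands.

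A reader might infer that the planned between-group comparison is diluted by half, or that the plan needs about four times the sample size of ANCOVA. The protocol supports neither. It never names the main effect as the test, and the four-fold figure sets ANCOVA against the main effect rather than the interaction. Against the interaction, ANCOVA gains precision and corrects no bias.

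A reader might also extend the halving to all seven outcomes. It does not carry over to comfort and satisfaction, which are rated at Week 3 and after fitting as well. If their Day 1 rating is the one before fitting and the effect is equal at Weeks 3 and 6, the main effect would average two thirds of it, not half.

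The remaining replies also have weight. The baseline t-tests bias nothing, because no later step depends on them. Percentage of variance is not the only planned output, since descriptive statistics are promised for every outcome. The important differences cited in section 3.1.1 describe the instruments and are not set as success thresholds. A separate analysis plan, not seen here, might name the test.

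What is left is that the protocol itself fixes the method, leaves the deciding effect open among three, and passes over a more precise analysis of data it already collects.

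**Conclusion.** The point holds as one of clarity and precision. Section 3.9 should name one test per hypothesis. If the group main effect were used for the outcomes measured only on Day 1 and at Week 6, the estimate would be halved and power at N = 32 would be 38%, against 81% for the interaction (f = 0.26, rho = 0.5). If the interaction is used, the analysis is valid but has more variance than necessary. At an assumed 1 SD difference, moving to ANCOVA raises power by 10 percentage points at rho = 0.5, by 18 at rho = 0.3 and by 3 at rho = 0.7. These sizes rest on the assumed correlation, equal SDs and 16 analysable participants per arm. This is a free improvement and not a bias that must be repaired.

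**What to change.** - **VAS pain, DASH and COPM:** make ANCOVA of the Week-6 score on group and baseline score the single test of the hypothesis. Report the adjusted mean difference with its 95% CI. It can then be read against the important differences cited in section 3.1.1: 12 mm for VAS pain, 10.83 points for DASH ("The minimal clinically important difference for the DASH is 10.83 points"), and 3.0 and 3.2 points for COPM performance and satisfaction. Percentage of variance has no direction or units and cannot be read this way.
- **Any outcome with a pre-randomisation baseline that stays in the mixed ANOVA:** state that the group-by-time interaction, not the group main effect, is the test.
- **Where ANCOVA should not be extended:** comfort and satisfaction have no meaningful baseline before a splint is worn. For the six-stage ordinal SST and the 0–10 triggering count, linear ANCOVA is no better suited than ANOVA.
- **Minor:** drop the baseline t-tests and describe baseline by group.

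The cost is a change of wording and one residual degree of freedom per ANCOVA. No extra data are needed.

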**c. Visual Analog Scale (VAS)**

The Visual Analog Scale (VAS) will be used to measure the participant's pain as well as comfort and satisfaction with splint wear in this study. VAS is a 10cm line that can be scored in either centimetres or millimetres (Dale et al. 2011). For pain, the left end of the VAS will be labelled as "no pain" and the right end "extreme pain". For comfort, the left end will be labelled as "not at all comfortable" and the right end will be labelled as "extremely comfortable". For satisfaction, the left end will be labelled as "not at all satisfied" and the right end will be labelled as "extremely satisfied". At the times of evaluation, each patient will be asked to make a mark on the line to indicate his/her rating for pain, comfort or satisfaction. The distance of this mark from the left end of the line will be measured. Thong et al. (2018) had reported that VAS pain scale had excellent internal consistency (Pearson's  $=0.93$ ) while Paungmali et al. (2012) reported that VAS had excellent test-retest reliability (Intraclass Correlation Coefficient, ICC= $0.90$ ). The minimal clinically important difference of the VAS pain scale is 12mm (Kelly 2001).

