## f. Canadian Occupational Performance Measure (COPM)

The Canadian Occupational Performance Measure (COPM) will be used to measure the participant's occupational performance. COPM, developed by the Canadian Association of Occupational Therapist, in collaboration with Health and Welfare Canada (Law et al. 1990), is a widely known interview-based assessment tool for measuring occupational performance. COPM uses a client-centered approach and requires the patient to report the types of activities that he/she is unable to accomplish and later, prioritize the meaningfulness and importance of the selected activities. During the interview, the patient must report and rate the satisfaction and the performance of the activities in three occupational therapy areas, i.e., self-care, productivity, and leisure. The importance, satisfaction, and performance of an activity are rated using a 10-point rating scale. A benefit of the COPM is that self-perceived changes in occupational performance problems can be assessed over time (Law et al. 1990). Berardi et al. (2019) found that COPM has good construct validity (Cronbach's  $\alpha=0.89$ ) and excellent test-retest reliability for the performance subtest (ICC=0.99) and the satisfaction subtest (ICC = 0.98). The minimal clinically important difference of the COPM is 3.0 points and 3.2 points for performance subtest and satisfaction subtest, respectively (Tuntland et al.2016).

[figure not shown]

[figure not shown]

Figure 1.0 CONSORT flow chart. This figure shows the flow of patients through the trial according to the criteria recommended in the CONSORT Guidelines.

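### Section 3.9 fixes percentage of variance as the effect measure for Hypotheses 1–7 and plans no between-arm estimate with a confidence interval, so the inferential output cannot show whether an important difference is demonstrated, excluded or left open.

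*Protocol*

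**What the plan says.** Protocol section 3.9 sets the inferential method: "A Two Way Mixed-ANOVA, set at the significant level of 0.05 will be used to compare the assessment outcomes". It ends by naming what will be reported, and ties it in brackets to all seven hypotheses: "The results will show the percentage of variance in each effect regardless of size".

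The same section also plans descriptive output. On the demographic data it says "Data will be analysed and described in total numbers, mean, and the pattern of data", and on the outcomes "Descriptive statistics will also be used to demonstrate the assessment outcomes including DASH, COPM, VAS (pain, comfort, and satisfaction"), together with the triggering count and SST. It does not say that these summaries are given by arm. It names neither a difference between arms nor a confidence interval.

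Section 3.1.1 cites minimal clinically important differences in scale units for three instruments:

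- Pain: "The minimal clinically important difference of the VAS pain scale is 12mm".
- DASH: "The minimal clinically important difference for the DASH is 10.83 points".
- COPM: "The minimal clinically important difference of the COPM is 3.0 points and 3.2 points for performance subtest and satisfaction subtest, respectively".

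None is cited for SST, the triggering count, comfort or satisfaction. Section 3.9 does not refer to any of the three.

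**The concern.** The general objective (section 2.2.1) is to compare the effectiveness of two active splints. A reader of such a trial wants to know which splint did better, by how much, and how uncertain that is. Percentage of variance is built from the squared effect, so it discards the sign. It also divides by the spread of the data, so it loses the unit. A share quoted for each effect will also include the effect of time, which says nothing about which splint is better.

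This is a measure that the protocol states, not a detail it leaves open, and a later analysis plan that follows section 3.9 would inherit it. At stake is interpretation. In a trial of about 36 participants, a non-significant result may be fully compatible with a difference that patients would notice. A p-value beside a variance share does not reveal that.

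**Working it through.** **Inputs from the protocol.** Section 3.6 gives planning pain scores of 4.65 (SD 2.39) before and 3.40 (SD 2.44) after treatment, Cohen's d 0.5175152, f 0.259 (0.26 used), 32 participants before dropout, and 36 in total at 18 per arm. Section 3.1.1 gives 12 mm for pain on a 10 cm line, that is 1.2 cm.

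**Assumptions.** 32 evaluable participants, 16 per arm. The planning SD of 2.44 is read in centimetres. The baseline-to-Week 6 correlation ρ is not in the protocol, so a range is shown.

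**1. The plan's own figures.**
- d = (4.65 − 3.40)/√((2.39² + 2.44²)/2) = 1.25/2.415 = 0.518, and f = d/2 = 0.259. Both agree with section 3.6.
- For a group-by-time interaction with two groups, two times and assumed ρ = 0.5, the non-central F calculation at f = 0.26 gives 32 participants with power 0.812. Then 32/0.90 = 35.6, rounded up to 36. The sample size reproduces and is not in question here.

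**2. No direction.** For a two-arm contrast, share of variance = t²/(t² + N − 2).
- Standard error = 2.44 × √(2/16) = 0.863 cm.
- For +1.2 cm, t = 1.2/0.863 = 1.39 and the share = 1.935/(1.935 + 30) = 6.1%.
- For −1.2 cm, t = −1.39 and the share is again 6.1%.

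**3. No unit.** The same 12 mm difference in pain change gives these shares, by assumed SD of change (16 per arm):

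| SD of change (cm) | 1 | 1.5 | 2 | 2.415 | 3 | 4 |
|---|---|---|---|---|---|---|
| Share of variance | 27.7% | 14.6% | 8.8% | 6.2% | 4.1% | 2.3% |

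Conversely, a share of 6.3% on DASH would mean 5.0, 7.5 or 10.0 points at assumed SDs of 10, 15 or 20, in either direction. A share cannot be placed against a threshold in millimetres or points unless the SD and the sign are also given.

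**4. What an interval would show for pain.** The 95% half-widths are:
- Week 6 difference, unadjusted: 2.042 × 0.863 = 1.76 cm.
- Week 6 difference adjusted for baseline, 2.045 × 0.863 × √(1 − ρ²): 1.68, 1.53 and 1.26 cm at ρ = 0.3, 0.5 and 0.7.
- Difference in change, which is what the two-time interaction tests. SD of change = √(2.39² + 2.44² − 2ρ × 2.39 × 2.44) = 2.858, 2.415 and 1.871 cm. Half-width = 2.042 × SD × √(2/16) = 2.06, 1.74 and 1.35 cm at the same ρ.

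When the half-width exceeds 1.2 cm, any interval that contains zero must also contain +1.2 or −1.2.

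**5. Where that stops holding.** With 18 per arm and ρ = 0.7, the baseline-adjusted half-width is 2.035 × 2.44 × √(2/18) × √(1 − 0.49) = 1.18 cm. With 16 per arm and ρ = 0.8 it is 2.045 × 0.863 × 0.6 = 1.06 cm. A null result could then exclude 1.2 cm both ways, but only if the observed difference is within 1.2 − 1.18 = 0.02 cm or 1.2 − 1.06 = 0.14 cm of zero, respectively.

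**The case against.** The strongest reply is that section 3.9 does not confine the reader to a p-value and a variance share. It also plans descriptive statistics, including means. If these are given by arm, as is usual, direction and raw size can be read in scale units. That stands: a reader might infer from the quoted sentence that nothing else will be shown, and the text does not support this. But arm means alone give no uncertainty for the difference between arms, and that difference is what the seven hypotheses concern.

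A second reply is that a missing interval is normally left to an analysis plan, and that the closing words of the sentence may only mean that small effects will be reported too. That reading is plausible, and nothing here depends on the phrase. Silence alone would be no finding. The point is that the protocol does name an effect measure for its hypotheses, and the one it names does not answer its comparative objective.

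Third, the minimal important differences are cited for three of seven outcomes, so that part bears on Hypotheses 2, 4 and 5 only. They stand in the instrument descriptions, beside reliability coefficients, and not as between-arm decision limits. Both remarks are correct. Using them to read the intervals is a proposal, not a rule the protocol has broken.

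Fourth, interval width follows from sample size and correlation and would not change with the reporting sentence. True, but the interval is what makes that width visible.

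**Conclusion.** The point holds as one of reporting and interpretation. The lack of sign, unit and interval in the inferential output affects all seven hypotheses; comparison with a cited minimal important difference concerns pain, DASH and COPM.

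For pain, under the assumptions of 16 evaluable per arm and SD 2.44 cm, a difference of 12 mm either way is about 6% of variance. The baseline-adjusted half-width is 1.68 to 1.26 cm for correlations of 0.3 to 0.7. A null result may therefore well leave 12 mm open. A reader might go further and infer that the trial can never exclude 12 mm. The documents do not support that, because the correlation is not given and the half-width falls to 1.18 cm with 18 per arm at 0.7.

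Nor do they support inferring that the investigators intend to claim equal effectiveness: section 2.1 states hypotheses of difference, and the protocol gives no rule for a null result. The sample size and the type I error are unaffected.

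**What to change.** Replace the last sentence of section 3.9 with wording such as:

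> For each outcome, the RMG minus MCPJBG difference corresponding to the tested contrast (difference in change from baseline, or baseline-adjusted Week 6 difference) is reported with its 95% confidence interval. For SST, an ordinal effect measure with its interval is used. For pain, DASH and COPM, the interval is read against 12 mm, 10.83 points and 3.0/3.2 points. An interval that contains both zero and that value in either direction is reported as inconclusive.

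The protocol should choose one of the two contrasts before results are seen. SST is treated separately because it is a six-stage ordinal grading, for which a mean difference is a poor summary. Partial eta-squared may be kept as a supplementary column.

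The cost is a short change of wording: same data, same visits, same participants, and standard software output.
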